#### Randomization

We randomize the participants at the class level, and classes within schools are matched on the school level in order to obtain more comparable research conditions. Classes are randomly allocated to the experimental or control condition by means of repeated coin tossing. For each selection of matched classes within schools, classes are assigned to the experimental condition if the coin toss shows heads and to the control condition if the coin toss shows tails. The coin toss procedure is continued until all matched classes are assigned to a research condition, such that as many matched classes as possible are assigned to the experimental and control conditions. Randomization is carried out centrally, with two researchers present to monitor the procedure.

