### Sample Size Calculation

Effect sizes are difficult to estimate for the InCharge program because the program is newly developed. As school-based prevention programs generally have small effects [12], we based the estimation of the sample size on a small effect size (*d*=0.2) [29]. In order to reliably detect a small-sized effect in a two-sided test with a conventional significance threshold of *α*=.05 and a power of (1–*β*)=0.80, 393 students are required per condition. However, as students are nested in classes and the program is delivered to classes of students, observations of students in the same class are not independent. Therefore, the required sample size is corrected for clustering. Assuming an intraclass correlation of 0.025 and an average class size of 16 participating students, the required sample size increases to 560 students in 35 classes per condition. Calculations are made using the downloadable procedure “clustersampsi” from Stata (StataCorp).

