**Alcohol, snacking, and physical activity**				
	Actual behavior	X	X	X
	Intentions	X	X	X
	Attitudes	X	X	X
	Social norms	X	X	X
	Negative outcome expectancies	X	X	X
	Self-efficacy	X	X	X
	Perceived parental rules	X	—^b^	—

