### Statistical Analysis

The background variables of the students (eg, gender, age, and educational level) will be checked to assess whether these variables are successfully randomized across the experimental and control conditions. Unsuccessfully randomized variables will be included as covariates in further analyses to control for potential confounding. Our data have a multilevel structure because participants are nested within classes, and these classes are nested within schools. Therefore, participants in one class or school are more similar than participants in other classes or schools. To account for this potential dependency in the data, we will correct standard errors and parameter estimates for clustering.

In order to determine the effectiveness of the health intervention, an intention-to-treat procedure and completers-only framework will be used to analyze the data. An intention-to-treat analysis of the data implies that participants will be analyzed under the condition that they are initially assigned, whereas completers-only framework analyzes only participants who are present at all time points. Using multilevel analyses, the three behavioral outcomes (snack intake, physical activity, and alcohol use) will be compared between participants in the experimental condition and those in the control condition at posttest and follow-up to determine the effects of the program. In the experimental condition only, multilevel analyses will be conducted to investigate the influence of treatment integrity on the predictors of the three health behaviors at posttest and follow-up. For missing data in multilevel models, maximum likelihood estimation will be used. As self-regulation is an important concept in InCharge, we will test whether the potential effects of InCharge on the health behaviors are explained by self-control. Additionally, relations between interpersonal communication with teachers, friends, classmates, and parents (ie, frequency and valence) and health-related outcomes, such as a mediating role between the conditions and outcomes, will be tested. As the program is delivered by teachers, we will also test in the experimental condition whether teacher communication relates to the evaluations of the health intervention and the three behavioral outcomes, using structural equation modeling. For structural equation models, expectation maximization will be used to impute the data.

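### Baseline behaviour has no stated role in the between-arm comparisons, and covariates depend on an observed imbalance, so precision from a measurement already scheduled is given up

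*Protocol article*

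**What the plan says.** The Statistical Analysis section of the protocol article describes multilevel analyses in which the three behaviours "will be compared between participants in the experimental condition and those in the control condition at posttest and follow-up". On covariates it gives one rule. Background variables, with gender, age and educational level as examples, are checked across the arms, and those found not to be balanced enter the later models. The section mentions the baseline value of a behaviour neither as a covariate nor as one wave of a repeated-measures outcome.

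Table 1 (Data Collection), in the block on alcohol, snacking and physical activity, has a row "Actual behavior" that is ticked at baseline, posttest and follow-up. The Aim and Hypotheses section says that all three waves serve the evaluation, but gives baseline no place in a model.

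The Sample Size Calculation section has no term for baseline adjustment. It finds that "393 students are required per condition" before clustering and that "the required sample size increases to 560 students in 35 classes per condition" after it.

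**The concern.** Earlier drinking, snacking and activity are likely to be among the best predictors of the same behaviours a few weeks or months later. A comparison that ignores them leaves explainable variance in the error term and lets chance differences in baseline behaviour between the arms add noise to the estimate.

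The covariate rule does not repair this. Even if baseline behaviour is read as one of the background variables, it enters only when it happens to look unbalanced. Under randomization any imbalance in assignment is chance, and a covariate earns its place by how well it predicts the outcome, not by the difference observed. The rule also leaves the covariate set unknown until the data have been inspected.

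At stake is power that the trial could have from data it already plans to collect.

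**Working it through.** **Inputs from the Sample Size Calculation section.** Standardized effect d = 0.2 ("we based the estimation of the sample size on a small effect size"); alpha 0.05, two-sided ("in a two-sided test with a conventional significance threshold of"); power 0.80; ICC 0.025 and 16 students per class ("Assuming an intraclass correlation of 0.025 and an average class size of 16 participating students"). Allocation is taken as 1:1, which fits the planned 35 classes per condition.

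**Reproducing the plan's figures.**
- Unclustered: the normal formula for two means with d = 0.2 gives 393 per arm, as stated.
- Design effect: 1 + (16 − 1) × 0.025 = 1.375.
- 393 × 1.375 = 540.4, and 540.4 / 16 = 33.8, so 34 classes (544 students) under the normal approximation.
- With a t test on 2(k − 1) degrees of freedom for k classes per arm, 34 classes give 79.2% power and 35 give 80.3%. Hence 35 × 16 = 560, as stated.

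The stated figures therefore reproduce exactly, with no baseline term.

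**Unadjusted standard error.** SE = sqrt(2 × 1.375 / 560) = 0.0701 SD, on 68 degrees of freedom; power 80.3%.

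**Adding baseline.** Write r for the baseline-outcome correlation. The documents do not give it, so it is assumed over 0.3 to 0.7. Two cases bracket the gain under a linear model, with degrees of freedom kept at 68:
- Both levels: student-level and class-level variance each shrink by the factor 1 − r², so SE = sqrt(2 × 1.375 × (1 − r²) / 560).
- Within-class only: SE = sqrt(2 × [0.025/35 + 0.975 × (1 − r²)/560]).

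Example for r = 0.5, within-class only: 0.025/35 = 0.000714; 0.975 × 0.75/560 = 0.001306; the sum is 0.002020; doubled it is 0.004040; the square root is 0.0636.

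| r | Both levels: variance cut | SE | Power | Classes per arm for 80% | Within only: variance cut | SE | Power | Classes per arm for 80% |
|---|---|---|---|---|---|---|---|---|
| none | – | 0.0701 | 80.3% | 35 | – | 0.0701 | 80.3% | 35 |
| 0.3 | 9% | 0.0668 | 83.9% | 32 | 6% | 0.0678 | 82.8% | 33 |
| 0.5 | 25% | 0.0607 | 90.1% | 27 | 18% | 0.0636 | 87.3% | 29 |
| 0.7 | 49% | 0.0500 | 97.6% | 19 | 35% | 0.0566 | 93.6% | 24 |

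**Chance imbalance.** If the baseline behaviour has the same ICC, its between-arm difference also has an SE of 0.07 SD. With r = 0.5, a one-SE imbalance moves an unadjusted estimate by about 0.5 × 0.07 = 0.035 SD, against a target effect of 0.2 SD. The unadjusted standard error already allows for this, so it is avoidable noise and not bias.

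**The case against.** The strongest reply is that the article is silent on baseline adjustment and does not forbid it. It names posttest and follow-up as the times of comparison, not as the full content of the model. Its list of background variables is given as examples. Completers must be present at every wave, baseline included, and missing data in the multilevel models are handled by maximum likelihood; both would fit a three-wave model. A condensed article may also leave the covariate list to a fuller document. This stands to the extent that a reader who infers that baseline is excluded goes further than the text. It does not dispose of the point, because the article does state a covariate rule, and that rule, followed as written, makes adjustment depend on imbalance.

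Second, nothing here is invalid. An unadjusted randomized comparison is unbiased, the sample size reproduces, and 1216 students were enrolled against 2 × 560 = 1120 planned. That stands in full.

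Third, the gain is uncertain. No correlation is given. Baseline falls one week before the lessons and follow-up 12 weeks after the intervention, so r may be lower at follow-up than at posttest. The outcomes are numbers of occasions and drinks, for which the 1 − r² rule is approximate. Classes are matched and randomized within schools, "such that as many matched classes as possible are assigned to the experimental and control conditions", which already balances part of the between-school difference and may leave less class-level variance for baseline to explain. These points stand. They are why the within-class-only case and the value r = 0.3 are shown.

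Fourth, Table 1 is a schedule. It does not show that every student has a baseline value, and the plan itself anticipates absences.

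**Conclusion.** The point holds as a matter of precision. As stated, the analysis gives baseline behaviour no role and selects covariates by observed imbalance, although the behaviours are scheduled for measurement at baseline. Power for d = 0.2 would rise from 80.3% to between 82.8% and 83.9% at r = 0.3, between 87.3% and 90.1% at r = 0.5, and between 93.6% and 97.6% at r = 0.7. The lower figure in each pair assumes that baseline explains only within-class variance, the upper that it explains class-level variance as well. The gain is modest at r = 0.3 and substantial from about r = 0.5. All of this rests on an assumed r, the plan's ICC of 0.025 and class size of 16, and a linear model.

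A reader might infer that the effect estimates will be biased, that the trial is underpowered by its own calculation, or that the plan rules baseline adjustment out. The documents support none of these: the arms are randomized, 560 students in 35 classes per condition is correct without adjustment, and no sentence says that baseline is left out. The change is one the sponsor should make; without it the trial is still valid.

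**What to change.** In the Statistical Analysis section, prespecify the student's baseline value of the behaviour under analysis, together with its class mean, as a covariate in every between-arm model at posttest and follow-up, whatever the observed balance. Let this replace covariate selection by imbalance check; baseline characteristics can still be tabulated by arm for description.

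A model that conditions on baseline can drop students who lack that value, which matters for the intention-to-treat analysis. To keep them, fit one multilevel model to all three waves with a common baseline mean across arms, and estimate the arm difference at posttest and at follow-up. This is a close alternative to the covariate model, not an identical one, so the plan should say which of the two is the main analysis.

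Neither form needs new data or a larger sample. The cost is a change of analysis wording, best fixed before any between-arm result is seen, and with the covariate form a stated way of handling missing baseline values.

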**Program evaluation**				
	Teacher evaluation (student questionnaire)	—	X	—

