**Intervention evaluation**				
	Student questionnaire	—	X	—
	Student focus group	—	X	—
	Teacher interview	—	X	—

^a^Measurement performed.

^b^Measurement not performed.

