Additional measures are general self-control, assessments of various temptations, interpersonal communication about the three health behaviors and the intervention, and evaluation of the program and teacher. First, we assess self-control using an adapted version of the Brief Self-Control Scale [35], which assesses deliberative action and impulse control using the following items: “I am good at resisting temptations,” “I have a hard time breaking bad habits,” “I do certain things that are bad for me, if they are fun,” “I wish I had more self-discipline,” “People would say that I have iron self-discipline,” “Pleasure and fun sometimes keep me from getting work done,” “Sometimes I can’t stop myself from doing something, even if I know it is wrong,” and “I often act without thinking through all the alternatives.” Second, we assess the perceived strength of the temptations with respect to alcohol use, snack intake, and lack of physical activity, as well as the motivation to resist these behavioral temptations. Third, we operationalized interpersonal communication as the frequency of discussions about the intervention (intervention condition only) and the three health behaviors outside class, and how positive or negative adolescents talk about the intervention and these three behaviors. The conversational frequency and valence are separately asked for conversations with friends, classmates, parents, and the teacher who taught InCharge. Fourth, regarding the program evaluation, we assess student perceptions of both the teacher and the prevention program InCharge. The included teacher-related measure is teacher communication, which is operationalized as a selection of variables assessing teacher clarity, verbal immediacy, and content relevance [36-38]. Evaluations of the program consist of an affective (eg, fun) and cognitive component (eg, informative).

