### Practical Relevance

The InCharge study evaluates the effectiveness of the program, and its findings will help to further improve the program. The study also investigates whether including self-regulation as a key component in a school-based health intervention promotes healthier lifestyles among older adolescents. If findings reveal that improving self-regulation skills decreases unhealthy behaviors, such as alcohol use and snack intake, and increases healthy behaviors, such as physical exercise, the findings may aid the developers of health interventions in designing effective behavior change programs for older adolescents. In addition to the content of the intervention, investigating how teacher communication relates to the three health behaviors can provide information on how to communicate for a school-based health intervention. This information can be used to formulate communication guidelines in order to improve the delivery of school-based health interventions and, ultimately, healthier lifestyles. Promoting healthier lifestyles is especially important for older adolescents because unhealthy behaviors generally peak during late adolescence [4,5]. Finally, this study aims to provide information on how interpersonal communication during the intervention and outside the classroom could improve or hamper the effectiveness of school-based health interventions. These findings may help health care professionals in designing interventions that elicit desired conversations about health-related topics in order to stimulate healthier lifestyles.

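### A clustering correction alone leaves the teacher-communication coefficient a blend of student and teacher differences, so by itself it does not support guidelines for teachers

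*Protocol article*

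**What the plan says.** Under Outcomes (Questionnaire Data), the article says "we assess student perceptions of both the teacher and the prevention program InCharge", and continues: "The included teacher-related measure is teacher communication, which is operationalized as a selection of variables assessing teacher clarity, verbal immediacy, and content relevance". Table 1 lists both the teacher evaluation and the student evaluation of the intervention as student questionnaires given at posttest only. Behaviours are self-reported at baseline, posttest and follow-up.

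The Statistical Analysis section notes that students are nested in classes and classes in schools, and gives this remedy: "we will correct standard errors and parameter estimates for clustering". The test at issue is then announced as follows: "we will also test in the experimental condition whether teacher communication relates to the evaluations of the health intervention and the three behavioral outcomes". The method named is a structural equation model. The section mentions no separation of student-level from class-level relations.

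Under Practical Relevance, the Discussion says of the relation between teacher communication and the three behaviours: "This information can be used to formulate communication guidelines in order to improve the delivery of school-based health interventions".

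**The concern.** Assume one InCharge teacher per class. All students of a class then rate the same person. Differences between their ratings are differences between students: how each perceived the teacher, how much each liked the lessons, or how each was addressed. Only differences between classes can show that one teacher communicates better than another.

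Guidelines on how to communicate need the between-class relation. A clustering correction changes the precision of a coefficient, and may reweight it, but does not split it into its two parts. Students who enjoyed the lessons may rate both teacher and programme highly. The model could then report a clear teacher-communication relation even if classes with better-communicating teachers did no better.

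**Working it through.** **The plan's own figures.** The Sample Size Calculation uses d = 0.2, two-sided alpha 0.05 and power 0.80, which gives 393 per condition (reproduced). The design effect is 1 + (16 − 1) × 0.025 = 1.375, and 393 × 1.375 = 540.4. That is 34 whole classes, or 544 students. The article states 35 classes and 560 students, one class more. I use its 35 classes of 16.

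**Weight of each level in one coefficient.** Let ρ be the ICC of the teacher rating (total variance 1), K = 35 classes and m = 16 students. The expected sums of squares of the rating are:

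- between classes: (K − 1) × (1 + (m − 1)ρ) = 34 × (1 + 15ρ)
- within classes: K × (m − 1) × (1 − ρ) = 525 × (1 − ρ)

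In a pooled model the within-class slope has weight w = within / (within + between). A random intercept with outcome ICC 0.025 multiplies the between part by 0.975 / (0.975 + 16 × 0.025) = 0.709. The reliability of an observed class mean is R = 16ρ / (1 + 15ρ).

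| Assumed ρ | Between | Within | Within share, pooled | Within share, random intercept | R |
|---|---|---|---|---|---|
| 0.05 | 59.5 | 498.8 | 89% | 92% | 0.46 |
| 0.10 | 85.0 | 472.5 | 85% | 89% | 0.64 |
| 0.20 | 136.0 | 420.0 | 76% | 81% | 0.80 |
| 0.30 | 187.0 | 367.5 | 66% | 74% | 0.87 |
| 0.40 | 238.0 | 315.0 | 57% | 65% | 0.91 |
| 0.50 | 289.0 | 262.5 | 48% | 56% | 0.94 |

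The pooled shares are equal where 34 + 510ρ = 525 − 525ρ, so ρ = 491 / 1035 = 0.47. A random intercept moves the weight further towards the within-class part.

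**Illustration with no teacher-level relation.** Take a within-class slope of 0.3 and a true class-level slope of 0. The expected single coefficient is w × 0.3 + (1 − w) × 0.3 × (1 − R). At ρ = 0.10 this is 0.848 × 0.3 + 0.152 × 0.3 × 0.36 = 0.27. Simulation (1000 runs per setting) gave 0.27, 0.24 and 0.21 at ρ = 0.10, 0.20 and 0.30, significant in at least 99% of runs despite cluster-robust standard errors.

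**Weaker within-class relations.** These simulations again set the class-level relation to zero, with outcome ICC 0.05 and ρ from 0.10 to 0.30:

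- Within-class correlation 0.15 to 0.30: pooled coefficient about 0.13 to 0.28, significant in 72% to 100% of runs. The slope on observed class means was about 0.03 to 0.11, significant in 6% to 11%.
- Within-class correlation 0.10: pooled coefficient significant in 41% to 53%.
- Within-class correlation 0.05: significant in 15% to 19%.

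A repeat with other random numbers stayed within about 0.01 on the coefficients and three percentage points on the rates.

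**Precision at class level.** By Fisher's z with 35 classes, the correlation detectable with 80% power is tanh((1.960 + 0.842) / √32) = tanh(0.495) = 0.46.

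**The case against.** The article does not say that the model has one level or one pooled slope. It recognises the nesting and promises to correct parameter estimates as well as standard errors. A two-level structural equation model may sit in an analysis plan that is not shown. This stands: the point is not that a detail is missing, but that the only remedy stated does not support the inference stated. A random intercept also counts as correcting the estimates, and it does not separate the levels.

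A reader might go further and infer that the coefficient mostly reflects halo or mood. The documents do not support that. They give neither an ICC for the ratings nor a halo correlation, and a within-class share is not a halo share. A teacher may really address students differently, and relevance of content may really differ between them. Perceived communication is also a legitimate construct at student level.

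Nor do the highest simulated rates carry over to the guideline sentence. Halo is most plausible for programme evaluation, rated by the same students at the same posttest. The Discussion names the behaviours, where shared-response bias should be weaker. The article also does not say which time point of the behaviours enters this model, so a same-day questionnaire effect cannot be presumed for them.

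Finally, the observed class mean is not a clean remedy: at ρ = 0.10, 36% of its variance (1 − 0.64) is within-class variation. Other evidence on teachers exists too, such as coded lesson observations and focus groups, although neither is named in this model.

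**Conclusion.** The point holds in limited form. A single coefficient for student-rated teacher communication, corrected for clustering, mixes student and teacher differences and by itself does not justify advice to teachers. The within-class part has the larger weight for any rating ICC below about 0.47 in a pooled model (about 0.85 of the weight at 0.10, 0.66 at 0.30). This rests on an assumed ICC, one teacher per class, and 35 classes of 16. Spurious significance ranges from modest (15% to 19% of runs at a within-class correlation of 0.05) to near certain (at 0.30). The upper end fits programme evaluation better than behaviour. This is a secondary aim within the experimental condition; the comparison of InCharge with control is untouched. It is worth correcting because the remedy is cheap and the stated use concerns teachers.

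**What to change.** State that this structural equation model has two levels, with a latent class mean of the teacher rating. Otherwise, enter the observed class mean and each student's deviation from it as two predictors. Report the within-class coefficient as perceived communication. Rest statements about teachers, and any guideline, on the class-level coefficient with its interval. The observed teaching style could be set beside it.

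The cost is analysis wording and at most one derived variable, with no new data. The class-level estimate rests on about 35 classes (fewer independent teachers if one taught several) and will be imprecise. The latent mean is preferable, because an observed mean of about 16 ratings still carries some within-class variation; with few classes its interval will be wide.

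### EM imputation for the structural equation models, with no stated allowance for imputation uncertainty, makes standard errors too small in the teacher-communication analysis

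*Protocol article*

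**What the plan says.** The Statistical Analysis section of the protocol article names two ways of handling missing data, by model type:

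- Multilevel models, which carry the comparison of the two conditions on snack intake, physical activity and alcohol use: "For missing data in multilevel models, maximum likelihood estimation will be used".
- Structural equation models: "For structural equation models, expectation maximization will be used to impute the data".

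The one analysis expressly assigned to structural equation modeling is confined to the experimental condition. It tests "whether teacher communication relates to the evaluations of the health intervention and the three behavioral outcomes, using structural equation modeling".

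Two further analyses are planned without a model type. On self-control: "we will test whether the potential effects of InCharge on the health behaviors are explained by self-control". On interpersonal communication, the relations with health outcomes, "such as a mediating role between the conditions and outcomes, will be tested".

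The only adjustment to standard errors that the section states concerns the nesting of students in classes and schools: "we will correct standard errors and parameter estimates for clustering". It gives no number of imputations, pooling rule or bootstrap. No expected missing fraction appears anywhere in the article.

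**The concern.** Imputing by EM usually means replacing each missing value by its conditional mean given the observed values. These values lie exactly on the fitted surface, so they add no residual variation, yet each counts as a full observation. The residual variance is understated, and in some patterns the information on the predictor is overstated as well. Adding a random residual to a single imputation reduces the problem but does not remove it, because the imputed values are still treated as known.

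What is at stake is the set of paths from teacher communication to program evaluations and to the three behaviors. The Practical Relevance section says that what is learned about teacher communication can be used to write communication guidelines. Paths declared significant too often would feed into those guidelines.

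Missing values are to be expected. There are three questionnaire waves, the last 12 weeks after the program, and the article plans a separate analysis of students present at all of them.

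**Working it through.** **Inputs.** From Sample Size Calculation: 560 students in 35 classes per condition, average class size 16, intraclass correlation 0.025, and testing "in a two-sided test with a conventional significance threshold of *α*=.05 and a power of (1–*β*)=0.80". From Table 1: the student questionnaire on the teacher and on the program is given at posttest only; the three behaviors are measured at all three waves. The missing fraction f is an assumption, taken from 5% to 30%.

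**The plan's own figure.** The article gives no figure for missing data, so only the sample size used below can be reproduced.
- Unclustered: 2 × (1.960 + 0.842)² / 0.2² = 392.5, rounded up to 393 per condition, as stated.
- Design effect: 1 + (16 − 1) × 0.025 = 1.375, and 393 × 1.375 = 540.4. Divided by 16 this is 33.8, so 34 classes.
- With a t reference on 2(k − 1) degrees of freedom, power is 79.2% at k = 34 and 80.3% at k = 35. That gives 35 classes, or 560 students, as stated.

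**Effect on one path.** Take a regression slope with true value zero, values missing completely at random, conditional-mean imputation and no auxiliary variables. Let S be the predictor sum of squares among the observed students and σ² the residual variance. In both cases below the estimate is the complete-case slope, whose true standard error is √(σ²/S). Imputed points have zero residual, so the completed file gives a residual variance of (1 − f)σ².

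*Case A: predictor and outcome missing together.* This fits a student absent at posttest, who lacks both the teacher and the program ratings. Imputed points sit at the means and add nothing to S. The reported SE is √((1 − f)σ²/S), so reported/true = √(1 − f).

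*Case B: outcome missing, predictor observed.* This fits a path to follow-up behavior. The completed predictor sum of squares is S/(1 − f). The reported SE is √((1 − f)²σ²/S), so reported/true = 1 − f.

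The rejection rate of a nominal 5% test is 2 × [1 − Φ(1.96 × ratio)]:

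| f | Case A ratio | Case A rejects | Case B ratio | Case B rejects |
|---|---|---|---|---|
| 5% | 0.975 | 5.6% | 0.95 | 6.3% |
| 10% | 0.949 | 6.3% | 0.90 | 7.8% |
| 20% | 0.894 | 8.0% | 0.80 | 11.7% |
| 30% | 0.837 | 10.1% | 0.70 | 17.0% |

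**Simulation checks (n = 560).**
- Case A, 4,000 runs: 6.7%, 8.2% and 11.0% at 10%, 20% and 30% missing. With an auxiliary correlated 0.5 with the outcome: 6.6%, 10.1% and 12.5%.
- Case B, 2,000 runs in a four-variable model: 6.3%, 8.0%, 10.9% and 18.6% at 5%, 10%, 20% and 30%. A single imputation with a random residual still gave 6.2%, 8.2%, 10.0% and 13.9%. Complete-case analysis of the same data stayed between 4.2% and 5.3%.

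**Does the planned clustering correction repair this?** The article does not say which correction will be used. Suppose it is a class-level sandwich estimator.
- In Case B it does not help. Imputed points add nothing to the residual part but still enlarge the predictor sum of squares, so the ratio stays at 1 − f. A simulation with 35 classes of 16, intraclass correlation 0.025 and cluster-robust standard errors rejected 5.2% with no missing data, then 6.5%, 7.9%, 11.8% and 17.0% at 5%, 10%, 20% and 30% missing.
- In Case A without auxiliaries, imputed points add nothing to either part. The sandwich then equals the complete-case one, and the ratio returns to 1. The Case A figures above therefore apply to model-based standard errors.

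**The case against.** Several points on the other side are fair.

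- **Single imputation is inferred.** The article does not say one completed file, nor conditional means, and it condenses a fuller plan. EM-based multiple imputation is not excluded. This stands as a caveat. However, the sentence fixes a method and nothing in it points to multiple imputation.
- **The reach is narrow.** A reader might infer that the trial's mechanisms aim as a whole is compromised. The documents do not support that. The Aim and Hypotheses section frames that aim around self-regulation and interpersonal communication, and no model type is named for either mediation test. Teacher communication is introduced separately, as an additional question.
- **The main result is untouched.** The comparison of conditions uses multilevel models with likelihood estimation and fills in no values. The affected analysis is a non-randomised association within one arm.
- **Two methods are not a contradiction.** A reader might infer that EM and maximum likelihood are incompatible in one dataset. They are not: EM is an algorithm for maximum likelihood, and the two rest on the same missing-at-random assumption. The fault is in analysing the filled-in file as observed data.
- **The size may be small.** At 5% missing the inflation is slight. The larger Case B figures do not suit paths between two posttest ratings, where Case A applies and a sandwich correction could largely remove the problem. Case B remains relevant for paths to follow-up behavior.

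**Conclusion.** The point holds in a limited form. As written, the plan treats EM-imputed values as observed in the structural equation models and states no allowance for their uncertainty. Standard errors for the teacher-communication paths would be too small. The self-control and interpersonal-communication mediation tests share the fault only if they too are fitted as structural equation models.

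The true error rate of a nominal 5% test ranges from close to nominal at 5% missing to about 10% (both variables missing together) or 17% (outcome only) at 30% missing. These figures assume a single imputation, values missing completely at random, no auxiliary variables and, for the lower figure, model-based standard errors. The missing fractions are assumptions.

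This should be fixed, but it is not a condition for the trial's main conclusion to be valid.

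**What to change.** Replace the EM sentence with, for example: *Structural equation models will be estimated by full-information maximum likelihood on the incomplete data, with the clustering correction already planned.* This also brings these models into line with the likelihood approach chosen for the multilevel models. Multiple imputation that respects the class structure, with pooled standard errors, is an acceptable alternative. If multiple imputation was intended all along, saying so and stating the pooling is enough.

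It would help to state in the same place whether the mediation tests are structural equation or multilevel models, so that the reader knows which missing-data rule governs them.

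The cost is one sentence and somewhat wider intervals. No new data are needed and the design does not change.
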